## PEACOCOC

---

treatment discontinuation. For patients who have not died or progressed, second progression-free survival will be censored at the date of last contact.

Kaplan-Meier survival methods will be used.

### **18.2.2.3. Overall survival**

Overall survival is defined as the time from start of treatment to death from any cause. All deaths will be included, whether they occur on study or following treatment discontinuation. For patients who have not died, overall survival will be censored at the date of last contact.

Kaplan-Meier survival methods will be used.

### **18.2.2.4. Objective response at 12 weeks and best objective response**

Objective response is defined as a complete or partial response as determined by RECIST v1.1. Patients without a tumour assessment at 12 weeks will be considered to be non-responders. The proportion of patients with objective response at 12 weeks will be presented as a proportion with 90% two-sided confidence interval.

The best objective response consists of the best among all objective responses assessed. Best objective response will be reported as a proportion with 90% two-sided confidence interval. The analysis of best objective response will be performed with all patients over the whole study period (including Re-treatment phase). A subset analysis will be performed for patients in the Re-treatment phase, once over the whole study period and once over the Re-treatment phase only.

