## PEACOC

---

Response or progression in the re-treatment period will not be considered part of the primary endpoint in this trial, time to second progression for these patients is included in the secondary endpoints.

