## PEACOCC

---

- Objective response rate at 12 weeks, and best objective response rate over the entire study and within the re-treatment phase.
- Duration of response over the entire study and within the re-treatment phase.
- Assessment of adverse events.
- QoL – FACT-O.
- Time to second progression in patients re-treated with pembrolizumab.

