### 9.3.3. Re-treatment Period

Re-treatment as part of this study is only available for a maximum of one year if the patient meets the following conditions:

- Either, the patient
  - Stopped initial treatment with pembrolizumab after attaining an investigator-determined confirmed complete response (CR) according to RECIST v1.1, and
    - Was treated for at least 24 weeks with pembrolizumab before discontinuing therapy
    - Received at least two treatments with pembrolizumab beyond the date when the initial CR was declared

**OR**

- Had SD, PR or CR and stopped pembrolizumab treatment after 24 months of study therapy for reasons other than disease progression or intolerability

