### AND

- Experienced a confirmed radiographic disease progression according to RECIST v1.1 after stopping their initial treatment with pembrolizumab
- Did not receive any anti-cancer treatment since the last dose of pembrolizumab
- Has a performance status of 0 or 1 on the ECOG Performance Scale
- Demonstrates adequate organ function as detailed in Section 7.2.1.
- Female patient of childbearing potential should have a negative urine or serum pregnancy test within 72 hours prior to receiving retreatment with study medication.
- Female patient of childbearing potential should be willing to use a highly effective form of contraception as detailed in section 7.3.1.
- Does not have an ongoing history or current evidence of any condition, therapy, or laboratory abnormality that might interfere with the patient's participation for the re-treatment period and full duration of the trial or is not in the best interest of the patient to participate, in the opinion of the treating investigator.

Patients who restart treatment will be retreated at the same dose and dose interval as when they last received pembrolizumab.

Permanent discontinuation of re-treatment is required if any of the following occur:

- documented and confirmed disease progression by RECIST v1.1 criteria
- unacceptable adverse event(s)
- intercurrent illness that prevents further administration of treatment
- investigator's decision to withdraw the patient
- patient withdraws consent
- pregnancy of the patient
- non-compliance with trial treatment or procedure requirements.

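### Best objective response in all patients includes the re-treatment phase and has no initial-course version, so it can overstate, and never understate, the response rate of initial pembrolizumab

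*Protocol*

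**What the plan says.** Protocol section 4.2.2 lists, among the secondary endpoints, "best objective response rate over the entire study and within the re-treatment phase". Section 18.2.2.4 turns this into an analysis. The definition is "The best objective response consists of the best among all objective responses assessed", and the scope is "The analysis of best objective response will be performed with all patients over the whole study period (including Re-treatment phase"). The section adds: "A subset analysis will be performed for patients in the Re-treatment phase, once over the whole study period and once over the Re-treatment phase only". It plans no other best-response analysis.

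Section 9.3.3 sets out who can be re-treated. There are two routes:

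- "Stopped initial treatment with pembrolizumab after attaining an investigator-determined confirmed complete response (CR) according to RECIST v1.1, and" (with further conditions on length of treatment);
- "Had SD, PR or CR and stopped pembrolizumab treatment after 24 months of study therapy for reasons other than disease progression or intolerability".

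Both routes also require that the patient "Experienced a confirmed radiographic disease progression according to RECIST v1.1 after stopping their initial treatment with pembrolizumab". Section 8.1.2.1 requires new RECIST-assessable scans before re-treatment registration.

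For the primary endpoint, section 4 takes the opposite line: "Response or progression in the re-treatment period will not be considered part of the primary endpoint in this trial".

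**The concern.** A best objective response rate in a single-arm trial is normally read as the proportion of patients whose tumours responded to the treatment as first given. Here the all-patient rate covers two courses separated by a documented progression. Someone who never responded in the initial course gets a second chance to be counted, and only selected long-term patients have that chance.

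The rate will be read against outside figures. Section 3.1.1 says the study will assess the objective response rate of pembrolizumab, and section 2.1.1 cites second-line chemotherapy response rates as low as 0–8% in clear cell ovarian cancer. Against a benchmark that low, one or two extra responders are visible. If the protocol is followed as written, no analysis gives the all-patient initial-course rate that such a comparison needs.

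**Working it through.** **The plan's own figure.** The protocol gives no expected value for best objective response. Its only design calculation is for the primary endpoint (section 18.1): 15% versus 33% progression-free at 12 weeks, one-sided 5%, 90% power, 48 patients, success if 12 or more are progression-free. With exact binomial tails, P(X ≥ 12 | n = 48, p = 0.15) = 0.0478 and P(X ≥ 12 | n = 48, p = 0.33) = 0.911. An exact search finds 48 to be the smallest sample size that meets both targets. The design reproduces, and nothing below touches it.

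**Direction of the difference.** Let x be the number of patients who respond in the initial course before first progression. Let k be the number who respond only later, on re-treatment.

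- Initial-course rate = x/48.
- Rate as planned = (x + k)/48.
- Difference = k/48, which is zero or positive because k cannot be negative.

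Each such patient adds 1/48 = 2.08 percentage points. The denominator of 48 is the target accrual and assumes it is met.

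**Who can contribute to k.** Patients re-treated after a confirmed CR are already responders. So are those who completed 24 months with a PR or CR. Only a patient whose best initial response was stable disease, who completed 24 months, later progressed, met the remaining section 9.3.3 conditions and then responded can add to k through re-treatment.

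**Size.** The protocol gives neither x nor k, so both are assumed below. Intervals are exact (Clopper–Pearson) two-sided 90%, the confidence level the protocol plans.

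| Assumed x | k = 0 | k = 1 | k = 2 | k = 4 |
|---|---|---|---|---|
| 5 | 10.4% (4.2–20.7) | 12.5% (5.6–23.2) | 14.6% (7.1–25.7) | 18.8% (10.1–30.4) |
| 10 | 20.8% (11.8–32.8) | 22.9% (13.4–35.1) | 25.0% (15.1–37.3) | 29.2% (18.6–41.8) |

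The k = 0 column is the initial-course rate. The k = 4 column is included for range and is not a forecast.

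**Can k be recovered from the planned outputs?** Only as an upper limit. It cannot exceed the number of responders reported for the re-treatment phase alone. That output does not separate patients who also responded initially from those who did not. The whole-study rate in the re-treated subset does not separate them either.

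**The case against.** The strongest defence is that this is a declared choice. Sections 4.1.2, 4.2.2 and 18.2.2.4 all say that best response covers the entire study, so nobody is misled about the scope. It is one of several secondary endpoints, and no decision rule or sample size rests on it. CR and PR patients already count, so the affected group is narrow: the design assumes only 33% progression-free at 12 weeks, about 16 of 48 (0.33 × 48 = 15.8), and 24 months of stable disease is much rarer ground. In the table, a shift of two patients stays inside the 90% interval of the initial-course rate. The 12-week response rate is an all-patient figure that re-treatment cannot affect.

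Most of this stands, and it limits the size of the point. It does not remove it. Disclosing the scope does not supply the missing initial-course estimate. The 12-week rate is no substitute: under section 10.3.1 scans continue every 12 weeks after week 12, so an initial-course response first seen at a later scan is absent from it. A shift inside the confidence interval is still a one-directional bias in the point estimate.

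A reader might infer several stronger things that the protocol does not support:

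- *That the rate does overstate.* The text shows only that it can; k may be zero.
- *That re-treatment response is measured from a new, larger baseline.* New scans are required, but no section says which scan is the reference for the all-patient analysis.
- *That responses after unconfirmed progression (section 16.1.2) inflate the rate.* How these count depends on RECIST v1.1 and on derivation detail that an analysis plan commonly holds.
- *That duration of response (section 18.2.2.5) becomes contradictory.* For someone responding only on re-treatment, the next progression can end the clock. This too is mainly derivation detail.

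**Conclusion.** The point holds as a limited one. The all-patient best objective response pools the initial and re-treatment courses, has no cut-off at first progression, and has no all-patient version confined to the initial course. As an estimate of the initial course's response rate it can be too high and never too low, by 2.1 percentage points per patient who responds only on re-treatment. That figure assumes 48 analysed patients. The number of such patients is not given, is likely small and may be zero; if it is zero, the two rates coincide.

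A reader might take this to threaten the trial's main result. It does not. Section 4 keeps re-treatment outcomes out of the primary endpoint, the 48-patient design with its cut-off of 12 is unaffected, and so is the 12-week response rate. The change is still worth making, because it removes an avoidable upward bias from a rate likely to be compared with outside figures.

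**What to change.** In sections 4.2.2 and 18.2.2.4, define the main best objective response for all patients as the best response from start of treatment to the earlier of first RECIST v1.1 progression or new anticancer therapy, in the initial course. Keep the whole-study rate and label it supplementary. Keep the already planned re-treatment-phase analysis in the re-treated subset, and state which scan is its reference baseline.

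The cost is wording only: no new visits, scans or patients, since the data are already collected. The downside is that the main rate may be slightly lower. Settling this before analysis also avoids choosing between two rates once both are known.

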### **18.2.2.5. Duration of Response**

For patients with an objective response, duration of objective response (DoR) is defined as the time from initial complete or partial response to disease progression or death on study from any cause (defined as death within 110 days of the last study treatment), whichever occurs first.

For patients with disease control (objective response or stable disease maintained  $\geq 12$  weeks), duration of disease control (DoC) is defined as the time from start of treatment to disease progression or death on study from any cause (defined as death within 30 days of the last study treatment), whichever occurs first.

A subset analysis of DoR and DoC will be performed only in patients re-treated. This analysis will be performed once over the whole study period and once over the Re-treatment phase only.

Kaplan-Meier survival methods will be used, and patients will be censored at the date of last contact.

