#### **18.2.2. Analysis of secondary endpoints and secondary analyses**

##### **18.2.2.1. Progression-free survival**

Progression-free survival is defined as the time from start of treatment to progression or death from any cause (whichever comes first). All deaths will be included, whether they occur on study or following treatment discontinuation. For patients who have not died or progressed, progression-free survival will be censored at the date of last contact.

Kaplan-Meier survival methods will be used.

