##### **18.2.2.2. Time to second disease progression (Re-treatment period)**

Time to second disease progression refers to progression in those patients re-treated on trial after their first progression. It is defined as the time from diagnosis of first progression during or after their initial pembrolizumab therapy to second progression or death from any cause (whichever comes first), during or after their retreatment pembrolizumab. All deaths will be included, whether they occur during the re-treatment period or following

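### Section 18.2.2.5 counts deaths up to 110 days after last treatment for duration of response but only up to 30 days for duration of disease control, while PFS counts all deaths; progression-free deaths outside the windows are censored

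*Protocol*

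**What the plan says.** Protocol section 18.2.2.5 defines two durations in adjacent paragraphs. For patients with an objective response, DoR runs from first response to progression or "death on study from any cause (defined as death within 110 days of the last study treatment". For patients with disease control, "duration of disease control (DoC) is defined as the time from start of treatment to disease progression or death on study", where the latter means "death on study from any cause (defined as death within 30 days of the last study treatment". For both, "Kaplan-Meier survival methods will be used, and patients will be censored at the date of last contact".

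Section 18.2.2.1 has no such window: "Progression-free survival is defined as the time from start of treatment to progression or death from any cause (whichever comes first", and "All deaths will be included, whether they occur on study or following treatment discontinuation". Section 18.2.2.2 (time to second progression) likewise counts deaths during re-treatment and after it stops, and section 18.2.2.3 (overall survival) counts all deaths.

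No reason is given for either window or for the difference between them. The two lengths match the safety reporting periods in section 13: 30 days for adverse events (13.2.1) and 110 days for serious adverse events and events of special interest (13.2.2, 13.4).

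**The concern.** One term has two meanings within a single subsection, and neither matches the rule used for the other time-to-event endpoints. Responders also belong to the disease-control group, so the clash can occur within one patient: a death can end the response while disease control is treated as possibly still running.

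A patient who dies without progression has no further progression-free time. Treating that patient as censored assumes that the later course would have resembled that of the patients still at risk, which is false for someone who has died. The Kaplan-Meier estimate can then be too high. The trial has a single arm, so there is no control group in which the same distortion could cancel.

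**Working it through.** **Plan's own design figure.** Section 18.1 asks for at least 12 of 48 patients progression-free at 12 weeks, testing 15% against 33%. Exact binomial: P(X ≥ 12 | 48, 0.15) = 0.0478 and P(X ≥ 12 | 48, 0.33) = 0.9114. This agrees with one-sided 5% and 90% power. Nothing in it uses DoR or DoC, so the point below leaves it untouched.

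**Status of one death under the three rules.** Take a responder with disease control who dies without documented progression, and apply sections 18.2.2.1 and 18.2.2.5.

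| Days from last dose to death | PFS | DoR (110 days) | DoC (30 days) |
|---|---|---|---|
| 20 | event | event | event |
| 60 | event | event | censored |
| 100 | event | event | censored |
| 150 | event | censored | censored |

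DoC and PFS share their time origin and their progression event. The death window is the only difference between them in what counts as an event.

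**Can such deaths occur?** The end-of-treatment visit is at 30 ± 7 days (section 10.5). Patients who stop for reasons other than progression are then imaged every 84 ± 7 days after the end of treatment (section 10.6). The DoC window therefore closes at about the end-of-treatment visit, well before the first follow-up scan. A patient who deteriorates and dies between scans can lack a documented progression.

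**Size, by illustration.** The documents do not give the share of first events that are progression-free deaths (f) or the fraction of those deaths outside the window (q), so both are assumed. With a constant hazard and true median m, the all-deaths hazard is ln 2 / m. If a share f × q of events is censored instead, the hazard falls to (ln 2 / m)(1 − f × q), and the reported median becomes m / (1 − f × q). With m = 6.0 months (assumed):

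- f = 5%, q = 50%: 6.0 / 0.975 = 6.15 months
- f = 10%, q = 100%: 6.0 / 0.90 = 6.67 months
- f = 20%, q = 100%: 6.0 / 0.80 = 7.5 months

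For a given pattern of deaths, q is at least as large for DoC as for DoR, because the DoC window is shorter.

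**Direction.** A simulation of 2,000 data sets used 15 patients each, exponential times with mean 8.7 months, and a 20% chance that an event is a progression-free death outside the window (all assumed).

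- Censoring at the date of death: the windowed curve was never below the all-deaths curve.
- Censoring up to about 12 weeks before death, because the rule uses last contact: the 12-month estimate was on average 0.068 higher and was lower in 0.9% of data sets. In 760 of 2,000 (38%) the windowed curve was lower at one or more monthly time points.

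The bias is thus upward on average, but not at every time point of every curve.

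**The case against.** The case for leaving this alone, or ranking it low, has real force.

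- A death after documented progression changes neither duration, because progression is already the event. Confirmed progression is a listed reason to stop treatment, and patients who stop for other reasons stay on regular imaging. Progression-free deaths outside the windows may be few. This stands, and it limits the size.
- DoC is not among the listed endpoints in sections 1.1 and 4.2.2. DoR is one of several secondary endpoints, and PFS already gives an all-deaths result. This stands, and it limits the severity.
- A single justified window with an all-deaths sensitivity analysis would also be coherent. That is fair, but the section has two windows and justifies neither.
- A statistical analysis plan might settle the matter. The protocol, however, does not leave the rule open: it states two that conflict.

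Stronger readings are tempting but not supported:

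- A reader might infer that both durations are certainly inflated. That requires progression-free deaths outside the windows, and the documents give no count of them.
- A reader might infer that the DoC curve must lie on or above the PFS curve. Censoring is at last contact, which can precede death, and PFS is not restricted to patients with disease control.
- A reader might take a survival curve from last dose and read off how few deaths fall within 30 or 110 days. That curve describes all deaths, including those after progression, and does not estimate the share that matters.
- A reader might infer that the bias falls mainly on patients who stop in complete response or at 24 months. They remain on 12-weekly imaging, so outliving the window matters only if they then die without documented progression.

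**Conclusion.** The inconsistency is a fact of the text: two windows for one term, both different from the all-deaths rule of PFS, time to second progression and overall survival, and no other section reconciles them. Progression-free deaths outside the windows are censored informatively, which can bias the Kaplan-Meier DoR and DoC upward.

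The size cannot be derived from the protocol. The range from about 6.15 to 7.5 months against a true 6.0 rests on a constant hazard, censoring at the date of death and assumed shares of progression-free deaths; the true effect may be small. Only secondary analyses are touched. Severity is moderate.

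**What to change.** In both definitions in section 18.2.2.5, replace the on-study death and its window with death from any cause, as in section 18.2.2.1. If an on-study version is also wanted, use one window for both durations, give the reason for it, and label it a sensitivity analysis.

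The change is two phrases. It needs no new data: survival status is already followed to death, withdrawal of consent or end of study (section 10.6.1), and disease status is followed until progression, death or end of study (section 10.6). The cost is that the reported durations may become slightly shorter. The 48 patients and the cut-off of 12 do not change.

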**18.2.2.6. Quality of Life**

The questionnaire used will be FACT-O (version 4). QoL data will be analysed using methods for repeated measures. Descriptive statistics will be presented at each time point, as well as changes from baseline, for each subscale and overall. The algorithm for core construction will be based on that provided by the FACT-O manual.

**18.2.2.7. Safety Monitoring**

All patients who received at least one cycle of pembrolizumab will be included in the safety analysis. Adverse events (AEs) will be monitored on an ongoing basis and their frequencies reported. AEs will be categorized using the NCI Common Terminology Criteria for Adverse Events (CTCAE), version 5. The worst event for each patient will be described. Both events related and unrelated to treatment will be captured.

Clinical and laboratory data will be tabulated and compared to normal ranges for the institution.

**18.3. Interim analyses**

The study will be regularly monitored by UCL CTC, with input from members of the Trial Management Group. A report will be provided to the Independent Data Monitoring Committee (IDMC), who will review accrual, compliance, safety and efficacy. The first review by the IDMC will be triggered after 15 patients have completed the first CT scan assessment following the first cycle of pembrolizumab, and at least once each year thereafter. The IDMC will make recommendations on whether the trial should continue or stop recruitment, or the protocol modified. Any recommendation to stop the trial will be communicated to Trial Steering Committee (TSC).

